## Why is a trial needed now?

Obesity is increasingly prevalent in Western society.^20^ There are over 90 million obese individuals living in the United States alone, with over half of the population projected to be obese by 2030.^21^ The obese surgical patient has become unavoidable across all surgical specialties. In abdominal surgery, these patients can present unique problems due to increased intraoperative difficulty associated with both subcutaneous and visceral fat volume.^22–25^ ^26,27^Intraoperatively, obesity is associated with increased operative time, blood loss, and surgeon perceived technical challenge.^26^ Postoperative care can present similar difficulty, as obesity is associated with increased risk of surgical site infections, urinary tract infection, pulmonary complications, wound dehiscence, venous thromboembolism, and more.^7,27,28^ Obesity may even be associated with worse long-term oncologic outcomes following resection of solid tumors.^29,30^

In bariatric surgery, a surgical sub-specialty that almost exclusively manages patients with BMIs of greater than 35 kg/m^2^, patients undergo an intensive preoperative program to optimize both intra- and postoperative outcomes. Specifically with regards to preoperative weight loss, these patients adhere to VLEDs with liquid formulations, such as Optifast® or Modifast®.^31,32^ VLEDs are an intensive approach to short-term medical weight loss that include all recommended daily micronutrients and are fortified with protein, yet are limited in their fat and carbohydrate content, allowing them to promote weight loss while maintaining lean body mass.^33–35^ ^13^These preoperative programs are safe, tolerable, and have been associated with decreased fat volume, surgeon perceived operative difficulty, operative time, and postoperative LOS in patients undergoing bariatric surgery.^18,36^ Data supporting decreased postoperative morbidity with their use in bariatric surgery patients is less convincing. We conducted a systematic review and meta-analysis evaluating the impact of preoperative VLEDs in patients undergoing bariatric surgery in terms of postoperative morbidity.^14^ Data was pooled from four RCTs and there was a non-significant trend towards decreased postoperative morbidity (OR 0.65, 95%CI 0.35-1.19, p=0.16).^14^ This analysis was underpowered despite pooling. Nonetheless, current Canadian Adult Obesity Clinical Practice Guidelines and Enhanced Recovery After Surgery (ERAS) guidelines recommend two-to-three weeks of preoperative VLED with liquid formulations totalling 650-900 kilocalories (kcal) per day.^13^

Despite the advantages associated with preoperative VLEDs in bariatric surgery, the evidence associated with and use of preoperative VLEDs in other types of surgery remains sporadic. We recently performed a systematic review and meta-analysis that identified 13 studies evaluating the use of preoperative VLEDs in non-bariatric surgery.^19^ While data were heterogenous, preoperative VLEDs reliably resulted in significant weight loss (3.2-19.2 kilograms [kg]) and were well adhered to (94-100% compliance). In the seven included comparative studies, preoperative VLEDs were not associated with changes in postoperative morbidity, postoperative LOS, or operative time. They were not associated with adverse events or intolerance in obese patients with malignancy undergoing oncologic resection. Despite seemingly being safe and well tolerated, only four, small RCTs have evaluated their use for preoperative optimization of obese non-bariatric surgery patients.^37–40^ Altogether, there are significant grounds to explore the use of preoperative VLEDs in obese patients undergoing non-bariatric surgery as a means to optimize perioperative outcomes for this increasingly pervasive patient population. Moreover, our data pertaining to postoperative morbidity in bariatric surgery patients adds clinical equipoise to this patient-important outcome.

The current evidence base for preoperative VLEDs for obese patients prior to non-bariatric surgery is far from conclusive. Surgeon practice across the country is highly variable as a result. We are currently conducting a Canada-wide survey targeted at assessing current practice patterns in terms of preoperative weight loss interventions for obese patients undergoing non-bariatric abdominal surgery. Preliminary data suggest that most surgeons do not prescribe preoperative weight loss interventions to these patients, nor do they feel as though they foundational knowledge of the preoperative weight loss interventions currently available. Given the lack of high-quality evidence currently informing the use of preoperative VLEDs in this increasingly pervasive, and challenging, patient population, there is currently a highly justified basis for a large, high-quality, prospective trial to be conducted in this field. We have assembled a committed community of surgeons and solid trial infrastructure to pursue this endeavour and execute a large, definitive RCT aimed at assessing the efficacy of preoperative VLEDs for obese patients undergoing non-bariatric surgery.

## How will the results of this trial be used?

The feasibility and safety results of this pilot RCT will be used to inform the design and implementation of an adequately powered multi-center RCT aimed at assessing the efficacy of VLEDs at improving perioperative outcomes for obese patients undergoing non-bariatric surgery. We will use our pilot RCT as a platform to build further awareness about this omnipresent issue in contemporary surgery with the hope of recruiting physicians from other centers to participate in our definitive RCT. Ultimately, these data will inform the development of standardized and individualized preoperative optimization pathways for patients undergoing non-bariatric surgery for benign and malignant disease.

Both the findings of this pilot RCT as well as the overall trial will be published in peer reviewed medical journals and presented at international, national, and local conferences as part of our knowledge translation strategy. We will use these findings, in addition to other pertinent literature, to advocate for the creation of preoperative optimization guidelines for patients undergoing major surgery. We will liaise with large societies such as the Canadian Association of General Surgeons, Society of American Gastrointestinal and Endoscopic Surgeons, American Society of Colon and Rectum Surgeons, Enhanced Recovery After Surgery Society, and more for the development and dissemination of these guidelines. We have access to online platforms with reach spanning to surgeons across the world, such as OrthoEvidence and Cold Steele, that we will rely on to widely circulate these findings. Lastly, we will work with industry sponsors to create community outreach programs aimed at providing smaller, rural committees access to preoperative VLED products with the aim of enhancing preoperative optimization for obese patients undergoing surgery in all communities around the world.

## Are there any risks to the safety of participants involved in the trial?

Patients enrolled in this RCT will be randomized to receive either standard of care plus Optifast®/Medimeal® or standard of care alone. The standard of care arm would not be incurring incremental risk, though patients randomized to Optifast®/Medimeal® are at risk of mild and severe adverse events. Adverse events are listed in a separate document titled “Adverse Events”. The largest (n = 273) medical weight loss RCT utilizing Optifast® to date reports a mild adverse event rate of 76.8% and serious adverse event rate of 4.5% in patients enrolled in a yearlong program.^41^ The most commonly reported mild adverse events included constipation (18.7%), headache (17.4%) and dizziness (16.8%).^41^ Serious adverse events included symptomatic cholelithiasis, pyelonephritis, and seventh cranial nerve palsy.^41^ These data are most relevant to the long-term use of Optifast® and other similar VLEDs. In our systematic review the median intervention length was four weeks.^19^ Only one included study reported the occurrence of serious adverse events, at a rate of 7.8% over an eight-week intervention period.^37^ The remaining 12 studies in the systematic review, six of which included cancer patients, did not report serious adverse events related to liquid formulation weight loss products. Minor adverse events occurred in 0-50% of patients in the included studies, with only two studies reporting rates of greater than 14%.^37,42^ Both of these studies implemented VLED programs spanning eight weeks. Overall, while there are risks associated with VLED use, these risks are mostly limited to minor adverse events when used in the preoperative setting and we are confident that it will be a safe intervention for patients meeting inclusion criteria. Particularly given that the proposed duration of VLED in the present study is three weeks. There are no interactions with Optifast®/Medimeal® and prescribed medications that may put patients at risk. Overall, the risk associated with the use of Optifast®/Medimeal® in this trial should be minimal given that this product is already approved for this indication in this patient population.

# THE PROPOSED TRIAL

## What is the proposed trial design?

The proposed trial will be a multi-center, surgeon, outcome assessor, and data-analyst blinded, parallel pilot RCT.

## What are the planned trial interventions?

### Intervention Group

The preoperative VLED protocol will utilize Optifast® or Medimeal®, commercially available weight loss products. Specifically, the Optifast® 900 product will be used for this RCT. Patients will receive a three-week supply of Optifast® 900 or Medimeal®. They will be instructed to consume four packets of Optifast® 900 or Medimeal® mixed with water daily. This provides a total energy intake of 900 kcal per day. Patients will also be allowed to consume up to two-cups of low-calorie vegetables per day along with the Optifast® meal replacement product. They will be provided with a handout containing specific instructions with regards to the intervention (see “Very Low Energy Diet Instructions” document). The intervention group will receive the Optifast® 900 program or Medimeal®, as described above, in addition to standard of care for preoperative management.

Patients enrolled in the trial and assigned to the VLED group who are diabetics will be referred to a diabetes educator nurse practitioner for management of their insulin dosing and/or other anti-hyperglycemic medications throughout the duration of the intervention period.

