## What are the proposed practical arrangements for allocating participants to trial groups?

Patient recruitment will occur at Hamilton Health Sciences, St. Joseph’s Healthcare Hamilton, and Kingston Health Sciences. All surgeons who perform elective non-bariatric surgery at these sites will be made aware of the study via workshops and internal communications. Patients will be identified by the surgeons, their administrative assistants, and/or study investigators at the time of referral, at the time of their initial preoperative consultation, or some time following their initial preoperative consultation. Surgeons and/or other clinicians within a patient’s circle of care will introduce the study to participants at the time of their preoperative visits or sometime thereafter. Patients may also reach out directly to study investigators via the contact information provided on the study poster should they choose. Patients meeting inclusion criteria based on a review of their electronic medical record, which will only be accessed by persons within the circle of care or researchers that have obtained permission from the patient, will have their contact information (i.e., email and phone number) recorded and provided to designated research personnel at the time of their initial surgical consultation in clinic. This email contact information will then be passed into a novel automated clinical trials platform developed by Phelix AI©. This platform will automatically send an electronic version of the written informed consent document to the patient as well as a link to schedule an appointment in the following 1-2 days with the research team to discuss the informed consent document via telephone. If the Phelix AI© platform identifies that the patient does not have an accessible email address, this will trigger a notification to the research team and prompt them to call the patient by telephone. At the time of initial contact between the study personnel and patient, the study will be introduced, eligibility will be confirmed. Patients will be provided with the opportunity to ask questions about the previously circulated ICF, and if they have yet to review the document, they will review the document in its entirety with the research team at the time of the telephone contact. If, at the end of this process, patients are understanding of the material risks and benefits of participation, and wish to be enrolled in the study, they will sign the ICF and subsequently be randomized to one of the two arms in this parallel RCT. Following ascertainment of written informed consent, patients will be randomized via a web-based randomization system (randomization.net) in a 1:1 fashion to receive either standard of care plus preoperative VLED or standard of care alone. Randomization will be according to variable block sizes of four and six and will be stratified according to centre.

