The aforementioned automated clinical trials platform developed by Phelix AI© is a novel platform that automates the “patient research journey”. The research team will input the patient contact information into the Phelix AI© platform and the platform will then automatically start patients along their journey. The specific tasks that this platform will perform for the purposes of this trial include: 1) sending the ICF document; 2) scheduling a telephone follow-up with researchers to discuss the ICF document and complete the informed consent process; 3) send reminders to patients at the 1-week and 2-week points of the intervention period to remind patients to adhere to the study protocol; 4) schedule a post-intervention follow-up appointment with the research team; 5) send a follow-up email to patients two weeks after their scheduled surgery to ascertain whether any adverse events have occurred and whether they have required any care outside of the hospital in which they underwent their index operation; 6) schedule the 30-day postoperative visit with the research team. Neither this platform nor the company will retain or store any patient or research information asides from the patient email address for contact throughout the trial. Phelix’s network and services are cloud native (i.e., built on and benefit from the security measures provided by Google’s Cloud Platform (GCP)). Phelix classifies email address as Personal Data. All data, including Personal Data, is at all times hosted on Canadian servers and resources on Google Cloud Platform. Phelix does not access, share or process Personal Data beyond what is minimally required to enable customers access their Phelix services.  Email addresses used by your organization in its engagement with Phelix are not shared externally, and only shared internally on a need-to-know basis among the Phelix personnel (i.e., the researchers) with whom you will interact by email. Otherwise, at all times, whether in transit or at rest, email addresses are treated as any other Personal Data stored on Phelix, and will be anonymized, encrypted, and securely hosted.

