## What is the proposed duration of treatment period?

The current protocol in use at our local Bariatric Surgery Center of Excellence (i.e., St. Joseph’s Healthcare Hamilton) utilizes four doses of Optifast® 900 or Medimeal® daily and the total length varies between one and three weeks based on preoperative liver size and BMI. To standardize the approach for non-bariatric surgery, we propose an intervention period of three-weeks. Patients will start the intervention period three weeks and one day prior to their operative date, and the last day of the intervention will be the day prior to surgery. Our systematic review identified protocols varying from 0.46-26 weeks that were safe and efficacious, and thus we are confident that our intervention period is appropriate.^19^ Similarly, the current protocol in use at our local Bariatric Surgery Center of Excellence is in keeping with the findings of our systematic review in terms of VLED liquid formulation product and caloric intake target. In our systematic review and meta-analysis, Optifast® was the most commonly studied VLED liquid formulation (35.7% of included studies) and daily target caloric intake ranged from 450-1400kcal per day.^19^ As mentioned previously, the present study will also use the Optifast® 900 or Medimeal® and will aim to provide a total of approximately 900 kcal per day to participants.

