## What is the proposed frequency and duration of follow up?

Patients will attend follow up with their respective surgeons as per the surgeon’s clinical follow-up schedule for the given procedure. From a research perspective, the patient follow-up protocol will be implemented following initiation of the VLED. See Figure 1 for the SPIRIT diagram depicting the research follow-up protocol. Patients will be followed for a period of approximately 8 weeks. Patients will have in-person baseline measures, including weight, height, waist circumference, hand grip strength, and symptom screening at the time of preoperative VLED initiation, the day of their surgery, and at 30-days following the date of their surgery. On the day of their surgery, patient data will also be collected with regards to compliance with the preoperative VLED. At the one-month follow-up, patients will also complete standardized follow-up questionnaires that will focus on adverse events, symptoms, and postoperative recovery, as well as the 36-Item Short Form Survey (SF-36). Electronic medical records will be reviewed at thirty-days postoperatively to assess for postoperative morbidity and mortality. Both the clinical and research follow-up will be consistent regardless of the arm the patient is allocated to.

| **Activity** | **Before Randomization** | **-23** | **After Randomization** | | | |
| --- | --- | --- | --- | --- | --- | --- |
|  | **-60 to -23** |  | **-23 to -2** | **-2 to 0** | **0 to discharge** | **+30** |
| Eligibility assessment | X |  |  |  |  |  |
| Informed consent | X |  |  |  |  |  |
| Randomization |  | X |  |  |  |  |
| Intervention (i.e., VLED) |  |  | X |  |  |  |
| Baseline demographic data | X |  |  |  |  |  |
| Operative data collection |  |  |  | X |  |  |
| Baseline anthropometrics (including hand grip strength) | X |  |  |  |  |  |
| Post-intervention anthropometrics |  |  |  | X |  |  |
| Post-surgical anthropometrics |  |  |  |  |  | X |
| Intervention-associated adverse events |  |  | X | X | X | X |
| Postoperative morbidity |  |  |  |  | X | X |
| Surgeon perceived difficulty |  |  |  | X |  |  |
| QoL assessment (i.e., SF-36) | X |  |  | X |  | X |
| Intervention adherence |  |  | X | X |  |  |
| Follow-up completion |  |  |  |  |  | X |

*Figure 1.* SPIRIT figure for participant timeline

*VLED, very low energy diet; QoL, quality of life*

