4. Follow-up completion: Defined as completion of the pre-VLED, preoperative, and thirty-day postoperative visits, along with complete anthropometric measures and study questionnaires. A follow-up completion rate of greater than 90% will support the feasibility of a larger RCT. A follow-up completion rate of 80-90% will be considered feasible with modifications for the adequately powered RCT. A follow-up completion rate of less than 80% will suggest that a larger RCT is not feasible.

Safety Outcomes:

The primary safety outcome will be adverse events deemed secondary to the Optifast® 900 or Medimeal® programs. The adverse events will be recorded as dichotomous outcomes and described as either minor or serious, in a similar fashion to the OPTIWIN Study; the largest medical weight loss RCT evaluating Optifast®.^41^ Standardized definitions for minor and major adverse events are described in “Adverse Events” associated document. We will also measure patient frailty with grip strength at the time of anthropometric measurement.^43^

Clinical Outcomes:

The efficacy outcomes will include:

1. Overall 30-day postoperative morbidity. This will be defined as any deviation from the usual postoperative course within 30-days of the index operation and will be a composite of system-specific complications (see “Trial Outcome Definitions” document)
2. 30-day system-specific complications (see “Trial Outcome Definitions” document)
3. 30-day postoperative mortality
4. Preoperative weight loss. Preoperative weight loss will be assessed by measuring the post-VLED weight on the date of surgery and adjusting for the baseline weight in kilograms, as measured in a standardized fashion by a blinded research assistant.
5. Operative time. Operative time was chosen as an outcome as it is a commonly used objective surrogate for operative difficulty across various types of surgery.^44–46^ It has been used in previous bariatric RCTs as the primary outcome.^47^ Operative time will be measured as the time between first skin incision and closure of the last surgical wound in minutes and will be retrieved from the patient electronic medical record.
6. Intraoperative blood loss. This will be measured in milliliters and will be ascertained from the patient chart.

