## How will the outcome measures be measured at follow up?

The feasibility measures will be ascertained by the number of patients recruited and the number of patients completing follow-up as recorded on a standardized form by a research assistant, as well as patient reported compliance via a patient-completed diet diary that they will complete daily during the three-week period prior to surgery. Both the treatment and control arms will complete these forms and give them to the research assistant in an opaque envelope on the date of their surgery. Patients in the control arms will be instructed to leave the form blank.

Safety data will be ascertained via a combination of patient self-reporting and electronic medical record data. Paper and/or electronic questionnaires will be used to assess the presence of adverse events at baseline, the morning prior to surgery, and at 30-days postoperatively.

Similarly, efficacy data will be ascertained via review of the electronic medical record. Electronic medical records will be reviewed on the date of surgery and at 30-days postoperatively to assess for any further adverse events and to evaluate 30-day postoperative morbidity. We will assess operative time, intraoperative blood loss, and postoperative length of stay via electronic medical records. The quality-of-life data will be ascertained at baseline, following completion of the VLED, and at 30-days postoperatively via administration of an in-person paper or electronic SF-36 questionnaire. Lastly, anthropometric data (i.e., height, weight, waist circumference, grip strength) will be measured at baseline, the morning of surgery, and at 30-days postoperatively by a research assistant blinded to treatment allocation. This will be recorded and stored via a Redcap© form created *a priori*.

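### Medication review for diabetics is triggered only by assignment to the diet, and the schedule can leave 0 to 1 day before the first 900 kcal day

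*Protocol*

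**What the plan says.** Four parts of the Protocol bear on this.

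- **Referral.** The *Intervention Group* section states: "Patients enrolled in the trial and assigned to the VLED group who are diabetics will be referred to a diabetes educator nurse practitioner". The purpose is to manage insulin and other anti-hyperglycemic drugs for the whole of the diet period. No date is given by which the visit must happen, and it is not made a condition for the first packet. The diet is four packets a day, 900 kcal, with no step-down described.
- **Diet start.** Under *What is the proposed duration of treatment period?*: "Patients will start the intervention period three weeks and one day prior to their operative date", with the last diet day being the day before surgery. Figure 1, in the follow-up section, marks randomization in the day -23 column and the diet in the column running from day -23 to day -2.
- **Randomization.** The allocation section says that, once consent is given, "they will sign the ICF and subsequently be randomized to one of the two arms in this parallel RCT". Figure 1 allows consent between day -60 and day -23.
- **Risk statement.** The section on risks to participants says: "There are no interactions with Optifast®/Medimeal® and prescribed medications that may put patients at risk".

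The exclusion criteria name neither diabetes nor insulin use.

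**The concern.** A fall to 900 kcal per day is a reason to review insulin and other glucose-lowering doses, and the Protocol recognizes this by arranging the referral. The review protects the participant only if it is done before intake falls, or at the latest as it falls. Here the referral cannot be triggered before assignment, and the drawn schedule puts assignment on the first diet day or the day before. The timing works against the Protocol's own commitment to manage these drugs throughout the diet.

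What is at stake is first the safety of participants on glucose-lowering drugs. Safety of the diet is also the fifth feasibility objective, so a preventable gap in how the diet is delivered would affect something the pilot is meant to learn. A site looking to the risk section for guidance would find a general reassurance about prescribed drugs and no mention that glucose-lowering drugs may need reducing.

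**Working it through.** The Protocol states no lead time from assignment to diet start, so there is no figure to reproduce. The check is day arithmetic on its own schedule, with surgery as day 0.

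**Inputs**

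- Randomization: day -23 (Figure 1)
- Diet start by Figure 1: day -23, the opening of its column
- Diet start by the treatment-period section: 3 × 7 + 1 = 22 days before surgery, so day -22
- Consent window: day -60 to day -23 (Figure 1)
- Prescribed doses: 84, at four a day (outcome and intervention sections)

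**Lead time from assignment to first diet day**

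- Randomization as drawn, diet as drawn: -23 - (-23) = 0 days
- Randomization as drawn, diet as in the text: -22 - (-23) = 1 day
- Randomization straight after the earliest consent (day -60): -23 - (-60) = 37 days, or -22 - (-60) = 38 days

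The lead can thus lie anywhere from 0 to about 38 days. The lower end matters because consent is allowed up to day -23 and nothing sets a minimum. A same-day or next-day start complies with the Protocol.

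**Room for an earlier assignment**

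- Randomized by day -30, the lead is at least 30 - 23 = 7 days (Figure 1) or 30 - 22 = 8 days (text)
- Consent window: now 60 - 23 = 37 days; then 60 - 30 = 30 days; difference 7 days

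**Cost of a late review if packets are held**

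Surgery is on a fixed date and the compliance denominator is fixed at 84. Each diet day lost from the 21-day supply (84 / 4 = 21) removes 4 doses, and 4 / 84 = 4.8 percentage points of that participant's attainable compliance. The feasibility benchmark is a mean above 80%.

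**The two statements on drugs, side by side**

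The intervention section arranges drug management for diabetics because they are on the diet. The risk section says no interaction between the products and prescribed drugs may put patients at risk. Read narrowly, the second concerns a chemical or absorption interaction with the product, and both can be true. Read as an unqualified sentence in a section on participant risk, it pulls against the first. The wording does not tell the reader which is meant.

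**The case against.** The strongest reply is that the safeguard already exists. A commitment to manage drugs for the whole diet period includes day 1, so the lack of an explicit order of steps is not permission to start unmanaged. Adjacent columns in Figure 1 share their endpoints, so the 0-day gap may come from how the figure is drawn, and the allocation text allows randomization weeks earlier. The separate diet instructions, not at hand, may also set start conditions.

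Much of this is fair. The short lead is possible, not certain, and the 0 to 1 day is inferred from the schedule, not declared. It does not remove the point: the treatment-period text alone gives 1 day after a day -23 randomization, no minimum gap appears anywhere, and the commitment to manage drugs has no step that secures it before the first packet.

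A reader might infer three stronger things that the documents do not support:

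- **That the Protocol denies any medication risk.** The sentence speaks of interactions, and the same section says diet-arm patients are at risk of mild and severe adverse events.
- **That low blood glucose would be lost from the safety outcome.** It is true that "The primary safety outcome will be adverse events deemed secondary to the Optifast® 900 or Medimeal® programs", and that "questionnaires will be used to assess the presence of adverse events at baseline, the morning prior to surgery, and at 30-days postoperatively", so no questionnaire is scheduled during the diet. But Figure 1 marks adverse-event collection in the diet period, medical records are also used, the questionnaire before surgery can capture earlier events by recall, and an independent Data Monitoring Committee adjudicates events, with all serious ones collected. The *Adverse Events* definitions are not at hand.
- **That the number of patients or unreviewed days can be stated.** The Protocol gives neither the prevalence of diabetes nor the waiting time for the educator.

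**Conclusion.** The point holds as a gap in timing. The referral for glucose-lowering drugs follows assignment, the schedule permits 0 to 1 day between assignment and the first 900 kcal day, and no review is required before the first packet. This rests on Figure 1 and the treatment-period text as written, and on the absence of a minimum gap in the Protocol. The diet instructions, if they already require a review before starting, would reduce the point to bringing that rule into the Protocol.

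The risk-section sentence is a secondary matter of wording: it is in tension with the referral but does not strictly contradict it. The only size that can be given is the lead time. The change is still worth making before recruitment, because the hazard is foreseeable and the existing consent window has room for it.

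**What to change.** Keep the referral and change its timing.

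1. For participants on insulin or other glucose-lowering drugs, in either arm since use is known before assignment, randomize early enough within the day -60 to -23 window for the review to be completed, for example by day -30. Require the review to be recorded before the first packet is taken by those assigned to the diet. Amend Figure 1 to match.
2. Narrow the risk-section sentence to say that glucose-lowering drugs may need dose reduction on the diet and are managed as set out under *Intervention Group*.
3. Optionally, add a question on low blood glucose to messages already planned. At present the platform will "send reminders to patients at the 1-week and 2-week points of the intervention period to remind patients to adhere to the study protocol".

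The cost is protocol wording, a change to Figure 1, a case report form field for the recorded review and, if taken up, one message question. The consent window for these patients is 7 days shorter. Day -30 is an example: each site should check it against its own waiting time for the educator. If the review is still late, holding packets shortens the diet and lowers compliance against the fixed 84 doses, so early randomization has to carry most of the fix. The comparator, sample size and analysis are unchanged.
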